### Phase 2. Evaluation of the weight gain prevention guideline

The guideline is currently evaluated in a randomised controlled trial among 20 OPs including approximately 600 employees. Phase 2 describes the design of this trial, population, sample size and outcome measures, as well as a plan for adoption, implementation and evaluation (Step 5 and 6 of the IM protocol).

#### Study design

OPs were randomly assigned to the intervention or control condition by an independent researcher using Random Allocation Software (version 1.0, Isfahan University of Medical Sciences, Iran). Randomization of OPs took place before the baseline measurement, as the first counseling session of the intervention group took place directly after the baseline measurement. OPs in the intervention group were trained during two days in the guideline and associated intervention, including behavioral change counselling by a professional trainer. OPs in the control group were asked to provide care as usual. OPs were asked not to reveal their condition to participating workers. The study protocol was approved by the Ethics Committee of the VU University Medical Center.

#### Study population

OPs were recruited through a direct mailing by the Netherlands Society of Occupational Medicine to their member registry. OPs providing services to one or more companies of medium to large size (> 100 workers) and conducting preventive medical examinations were eligible to participate. OPs invited employees to participate via their usual channels (written letter, intranet, face-to-face in consultation hours). Inclusion criteria were: 1. unhealthy physical activity and/or dietary behavior and/or overweight, 2. currently not being on sick leave for 21 days or longer, 3. able to complete a Dutch questionnaire and 4. having signed an informed consent form. Unhealthy physical activity was defined as workers who do not meet physical activity guidelines [57]. Unhealthy dietary behavior was defined as workers who do not meet the Dutch national dietary guidelines for fruit- and vegetable consumption and fat [58]. Overweight and obesity were defined by a waist circumference larger than 94 cm and 102 cm respectively for men and larger than 80 cm and 88 cm respectively for women [59]. Obese workers could additionally be referred to the Dutch guideline for treatment of Obesity [60]. Workers were excluded when pregnant or in case a disease or condition was present which made physical activity impossible.

#### Sample size

The sample size was calculated according to the number of cases needed to identify an effect on waist circumference. Waist circumference was chosen over BMI as it is a more sensitive indicator of abdominal fat mass [61]. A previous study indicated that a difference in waist circumference of 1,5 cm between the intervention and control condition may be clinically relevant [43]. In an intention-to-treat analysis, 175 workers per condition are needed to detect a relative difference of 1,5 cm (standard deviation 4,5 cm) in waist circumference with a power of 80% and an alpha of 5%. As workers are clustered within OPs we adjusted for dependence of measurements with an intraclass correlation of 0.20. Taking a loss to follow-up of 20-40% into account among workers and OPs until the final measurement, the initial study population should consist of approximately 300 workers among 10 OPs in each study group (figure 4).

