#### Data analysis

The effectiveness of the weight gain prevention guideline will be analyzed after 6 months (short term) and after 18 months (long term) by means of multilevel analyses. Multilevel analyses accounts for the clustering of observations of workers within the same OP, as well as repeated measurements within one worker. Due to randomization at the OP level, short term data will be analyzed with two levels: 1. worker and 2. OP. Long term data will be analyzed with three levels: 1. time (3 follow-up measurements at 6, 12 and 18 months), 2. worker and 3. OP. Both crude and adjusted analyses will be performed. The multilevel analyses using the follow-up measurement (i.e. 6 months) as dependent variable will be adjusted possible confounders such as, gender, age and education. These variables will also be checked for effect modification. The long-term effect of the intervention will be analyzed using all three follow-up measurements (i.e. 6, 12 and 18 months) adjusted for possible confounders. Effect modification is checked. All statistical analyses will be performed according to an intention-to-treat principle. The investigator analysing the data is blinded to the randomization. A two tailed significance level of p < 0.05 is considered statistically significant. Analyses will be performed with SPSS 15.0 (SPSS Inc. Chicago, Illinois, USA) and MLwiN for multilevel statistical analyses.

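### 175 workers per arm cannot give 80% power at the stated ICC of 0.20 with 10 OPs per arm; on the plan's own inputs power is about 30-35%

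*Protocol article*

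**What the plan says.** The Sample size section sizes the trial on waist circumference: "175 workers per condition are needed to detect a relative difference of 1,5 cm (standard deviation 4,5 cm) in waist circumference", at 80% power and 5% alpha. The Data analysis section makes the test two-sided: "A two tailed significance level of p < 0.05 is considered statistically significant".

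On clustering, the Sample size section says: "As workers are clustered within OPs we adjusted for dependence of measurements with an intraclass correlation of 0.20". It gives no formula, design effect or cluster size for this step.

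On attrition it says: "Taking a loss to follow-up of 20-40% into account among workers and OPs until the final measurement". The resulting recruitment target is "approximately 300 workers among 10 OPs in each study group".

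OPs are the unit of randomisation (Study design) and the top level of the multilevel model (Data analysis). The ICC at OP level therefore governs the precision of the primary comparison.

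**The concern.** An ICC of 0.20 is large for clusters of this size. With 17 to 30 workers per OP it should multiply the sample size several times over, yet 175 is only modestly above what an individually randomised trial would need. With few clusters and a high ICC, the number of OPs limits precision much more than the number of workers does.

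Waist circumference is a primary outcome and the only one used for sizing. The article says that the guideline will be adapted on the basis of the effectiveness results and then disseminated nationally. If power is put at 80% when the plan's own assumptions give about a third, readers will take a null result as stronger evidence against the guideline than it is.

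**Working it through.** **Inputs.** Difference 1.5 cm, SD 4.5 cm, power 80%, alpha 5%, ICC 0.20, 10 OPs per arm, 175 workers per arm needed and about 300 recruited (all Sample size); two-sided test (Data analysis). My assumptions: 4.5 cm is the total SD, and clusters are of equal size.

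**1. Trying to reproduce 175.** Without clustering, n = 2 × (1.960 + 0.8416)² × (4.5/1.5)² = 141.3, so 142 per arm. Other settings do not give 175 either: one-sided 112, 85% power 162, 90% power 190. The ratio 175/141.3 is 1.24. At ICC 0.20, a design effect of 1.24 means 1 + 0.239/0.20 = 2.2 workers per OP. Using 0.20 as a flat factor comes near (141.3 × 1.2 = 170; 141.3/0.8 = 177), but the document does not show how 175 was obtained.

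**2. Design effect at the stated ICC**, 1 + (m − 1) × 0.20:
- 175 workers in 10 OPs, m = 17.5: 1 + 16.5 × 0.20 = 4.3; requirement 141.3 × 4.3 ≈ 608 per arm, about 35 OPs.
- 300 workers in 10 OPs, m = 30: 1 + 29 × 0.20 = 6.8; requirement 141.3 × 6.8 ≈ 961 per arm, about 32-33 OPs.

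**3. Is the ICC in the step from 175 to 300?** No. A 40% loss alone gives 175/0.6 = 292, which uses up that step. Even the whole route from 141.3 to 300 is a factor of 2.12, below 4.3.

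**4. Power for 1.5 cm at ICC 0.20, 10 OPs per arm.** Effective n = N / design effect; SE = 4.5 × √(2 / effective n). The t figures use 2 × (10 − 1) = 18 degrees of freedom.

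| Workers per arm | Effective n | SE (cm) | Power, normal | Power, t | Detectable at 80%, normal / t |
|---|---|---|---|---|---|
| 175 | 40.7 | 0.998 | 32.4% | 29.6% | 2.8 / 3.0 cm |
| 300 | 44.1 | 0.958 | 34.7% | 31.7% | 2.7 / 2.8 cm |
| unlimited | 50.0 | 0.900 | 38.5% | 35.1% | 2.5 / 2.7 cm |

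A simulation of cluster means gave 29.7% and 31.7% for the first two rows.

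**5. The ceiling.** As m grows, effective n tends to (OPs per arm)/ICC = 10/0.20 = 50, while 141.3 are needed. At ICC 0.20, 80% power needs more than 141.3 × 0.20 = 28.3 OPs per arm, whatever the cluster size.

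**6. If OPs are lost, within the stated 20-40%.**
- 8 OPs per arm, 175 workers: 27.8% (normal) or 24.8% (t, 14 df).
- 6 OPs per arm, 175 workers: 22.8% or 19.5% (t, 10 df).
- 6 OPs per arm, 18 workers each: 21.5% or 18.5%.

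**7. Which ICC would fit 175?** Solving 1 + 16.5 × ICC = 1.239 gives 0.0145. Power at 175 per arm (normal / t):
- ICC 0.02: 77.1% / 72.5%
- ICC 0.05: 63.6% / 58.9%
- ICC 0.10: 48.2% / 44.2%

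**The case against.** The best defence is that 0.20 may not be the OP-level ICC of the waist outcome as analysed. If the real value is near 0.01 or 0.02, the trial is close to its claim. This stands as a caution: the power figures are conditional on the printed ICC. It does not rescue the text, because 0.20 is then the wrong figure to print and the passage needs correcting anyway.

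A second defence is that baseline adjustment would shrink the residual SD. With the ICC still 0.20, 80% power (normal approximation) would need a residual SD of about 2.4 cm at 175 per arm or 2.5 cm at 300. The section states 4.5 cm and claims no such reduction.

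A reader might also infer three stronger points that the document does not support:
- *That loss was allowed for only once, leaving 108 workers per arm (300 × 0.6 × 0.6).* The wording can mean a combined range, and 20% at both levels leaves 300 × 0.8 × 0.8 = 192, above 175. The flow chart cited at this step is not available here, so its treatment of loss cannot be judged. What stands is that losing OPs lowers power further at ICC 0.20.
- *That the analysis uses a large-sample z cut-off.* Data analysis specifies multilevel models and states no reference distribution. The t figures here only bracket the answer; they differ from the normal ones by about 3 points at ICC 0.20 with 10 OPs per arm.
- *That the inflation of 1.24 reveals a particular mistake.* The route to 175 cannot be known.

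**Conclusion.** The point holds. The figures of 175 workers per arm, 80% power for 1.5 cm, SD 4.5 cm, ICC 0.20 and 10 OPs per arm cannot all be true. Given the stated ICC and a total SD of 4.5 cm, power is about 30-35% and cannot exceed about 38.5% however many workers each OP recruits. The difference detectable with 80% power is about 2.7-3.0 cm, nearly twice the target. These figures assume that no OP is lost and that clusters are equal in size; unequal sizes would lower power further.

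Two readings go too far. The document does not establish that the trial is severely underpowered in fact, because it does not settle whether the ICC or the power is the wrong entry. Nor does it follow that the trial could not detect 1.5 cm: power of 30-35% is low, not zero.

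**What to change.** Correct the Sample size section in one of two ways, with the formula 1 + (m − 1) × ICC shown:

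1. If 0.20 is the intended OP-level ICC, state that with 10 OPs per arm power for 1.5 cm is about 30-35% and the difference detectable with 80% power is about 2.7-3.0 cm. Say that OP loss lowers power further (about 25-28% with 8 OPs per arm, about 18-23% with 6).
2. If 0.20 is not the OP-level ICC for the analysed waist outcome, replace it with a justified value and give the resulting design effect and power. By normal approximation, 80% at 175 analysed workers per arm needs an ICC of about 0.014.

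In either case, interpret a null waist result against the restated power and the confidence interval.

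The cost is a reworded section and, under the first option, a much less favourable power statement. No new data are needed. OPs are already randomised and the evaluation is under way, so the practical remedy is disclosure and careful interpretation.

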**Figure 4 F4:**
[figure not shown]
Flow chart of the study population.

#### Measurements

Questionnaires are sent to employees prior to the initial health risk appraisal. Questionnaires are collected by OPs or their assistants during the health risk appraisal. Biomedical measurements are performed by trained OPs or their assistants following a standard protocol. Follow-up measurements take place after 6, 12 and 18 months.

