**Methods:**

Following the guideline development protocol of the Netherlands Society of Occupational Medicine and the Intervention Mapping protocol, the guideline was developed based on literature, interviews with relevant stakeholders, and consensus among an expert group. The guideline consists of an individual and an environmental component. The individual component includes recommendations for occupational physicians on how to promote physical activity and healthy dietary behavior based on principles of motivational interviewing. The environmental component contains an obesogenic environment assessment tool. The guideline is evaluated in a randomised controlled trial among 20 occupational physicians. Occupational physicians in the intervention group apply the guideline to eligible workers during 6 months. Occupational physicians in the control group provide care as usual. Measurements take place at baseline and 6, 12, and 18 months thereafter. Primary outcome measures include waist circumference, daily physical activity and dietary behavior. Secondary outcome measures include sedentary behavior, determinants of behavior change, body weight and body mass index, cardiovascular disease risk profile, and quality of life. Additionally, productivity, absenteeism, and cost-effectiveness are assessed.

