#### Primary outcome measures

##### Waist circumference

Waist circumference is measured as midway between the lower rib margin and the iliac crest to the nearest 0.1 cm [59,62]. Participants are measured in standing position without heavy outer garments and with emptied pockets, breathing out gently. To standardize waist circumference measurement, OPs or assistants were provided with a Seca 201 waist circumference measure (Seca, Hamburg, Germany). Additionally, waist circumference is measured in a random sample of workers (10-20%) at each measurement by an independent researcher.

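### Waist, the primary outcome that sets the sample size, is tape-measured by OPs who know their arm or by their assistants, who are not described as blinded, and the independent 10-20% re-measurement has no stated use

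*Protocol article*

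**What the plan says.** **Who measures.** Under Measurements: "Biomedical measurements are performed by trained OPs or their assistants following a standard protocol". Under Waist circumference: "OPs or assistants were provided with a Seca 201 waist circumference measure". That section also fixes the anatomical site, standing position, clothing and breathing, with readings to 0.1 cm.

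**Who knows the allocation.** OPs are the unit of randomisation. Under Study design: "OPs in the intervention group were trained during two days in the guideline and associated intervention", and "OPs were asked not to reveal their condition to participating workers". OPs therefore know their condition; the request protects only the worker's side. They were randomised before the baseline measurement. The Abstract adds: "Occupational physicians in the intervention group apply the guideline to eligible workers during 6 months". Step 4 of the guideline's development places the last of five counselling sessions at 6 months, which is also the first follow-up measurement.

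**Who is blinded.** Under Data analysis: "The investigator analysing the data is blinded to the randomization". No other study staff member is described as blinded.

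**The independent check.** Under Waist circumference: "waist circumference is measured in a random sample of workers (10-20%) at each measurement by an independent researcher". The article does not say what these readings are for or whether that researcher knows the allocation. The Data analysis section covers levels, adjustment, effect modification, time points and software, but not these readings.

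**Weight of the outcome.** Waist is listed with physical activity and dietary behaviour as primary. Sample size rests on it (1.5 cm, SD 4.5 cm), and the Economic evaluation relates costs to it.

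**The concern.** A tape reading depends on finding a midpoint, on tension and on the moment of expiration. An assessor who has counselled the worker on activity and diet, and who knows the arm, may read slightly differently from one in the control arm without intending to. The standard protocol and the supplied tape reduce random error and systematic differences in technique, but they do not separate the assessor from knowledge of the arm. Randomisation does not help, because the error arises after allocation and follows it. Nor does the multilevel model: a shift shared by one arm's assessors is indistinguishable from a treatment effect. Blinding the analyst comes after the readings have been made.

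At stake is the credibility of the one objectively measured primary outcome (the other two are questionnaires), and with it the cost-effectiveness ratio. The trial already collects data that bear on the problem, yet the article states no use for them, and the limitations in the Discussion do not mention unblinded measurement.

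**Working it through.** **Inputs from the article:** target 1.5 cm; SD 4.5 cm; 175 workers needed per condition; ICC 0.20; about 300 workers and 10 OPs recruited per arm; loss 20-40%; independent sample 10-20%. **Assumptions, not in the article:** differential reading error b = 0.25-1.0 cm; SD of the routine-minus-independent difference 1-3 cm, with 2 cm as the central value.

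**1. The plan's own figure.** 175/(1 - 0.40) = 292, which agrees with the planned 300 per arm. The 175 itself does not follow from its inputs: 2 × (1.96 + 0.84)² × (4.5/1.5)² gives 142 without clustering, and 142 × [1 + (17.5 - 1) × 0.20] = 611 with it. That is a separate matter; I use 175 below only as the article's stated analysis size.

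**2. Shift in the estimate.** The estimate moves by the full b at any sample size. 0.25/1.5 = 17%, 0.5/1.5 = 33%, 1.0/1.5 = 67% of the target.

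**3. Chance of a significant result with no true effect.** Φ(b/SE - 1.96) + Φ(-b/SE - 1.96).
- Ignoring clustering: SE = 4.5 × √(2/175) = 0.48 cm.
- With ICC 0.20 and 17.5 workers per OP: design effect 4.3, SE = 0.48 × √4.3 = 1.00 cm.

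| b (assumed) | no clustering | ICC 0.20 |
|---|---|---|
| 0.25 cm | 8% | 6% |
| 0.5 cm | 18% | 8% |
| 0.75 cm | 34% | 12% |
| 1.0 cm | 55% | 17% |

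**4. What the independent sample can show.** Workers remaining per arm: 300 × 0.80 = 240, or 300 × 0.60 = 180. Re-measured: 10-20% of 240 = 24-48; 10-20% of 180 = 18-36. The overall range is 18-48 per arm. The SE of the between-arm difference in reading error, per visit and before clustering, is SD × √(2/n):

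| SD (assumed) | n = 48 | n = 18 | 95% half-width |
|---|---|---|---|
| 1 cm | 0.20 | 0.33 | 0.40-0.65 cm |
| 2 cm | 0.41 | 0.67 | 0.80-1.31 cm |
| 3 cm | 0.61 | 1.00 | 1.20-1.96 cm |

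Only with an SD of 1 cm and a 20% sample (36-48 per arm) does the half-width fall below 0.5 cm, and that is before clustering. Reader error clusters by assessor, and 18-48 workers over about 10 OPs is roughly 2-5 per OP, so real precision is worse.

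**5. Cost of correcting the effect by arm.** Treating the two errors as independent, √(0.48² + 0.41²) = 0.63 and √(0.48² + 0.67²) = 0.82 cm, against 0.48 cm uncorrected. An arm-wise correction adds considerable noise.

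**The case against.** Several stronger readings are tempting, and the article does not support them.

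- *The counselling OP takes every waist reading, so the effect rests entirely on unblinded readings.* The text says OPs or their assistants. The assistants' share and their knowledge of allocation are not given. What remains is that assistants are not described as blinded or as independent of the OP's practice.
- *The independent readings have no role in the analysis.* Only the absence of a stated role is established. This is a journal article, and a full protocol or SAP may define one. Who measures the outcome, by contrast, is a design choice that the article itself states.
- *The estimate is biased towards benefit.* The article shows that bias is possible, not its sign or size. Benefit is the plausible direction, no more.
- *OPs set weight goals and so have a stake in the reading.* The programme objectives are activity, sedentary behaviour, fruit and snacks, and the worker chooses among target behaviours.
- *Nothing but the analyst's blinding protects the outcome.* Trained measurers, a fixed procedure, a supplied tape, the request that OPs not disclose their condition to workers, and a random independent check are real partial safeguards.

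It can also be said that the check is too small to rescue the estimate. That stands, and it limits what the remedy may claim. Moving the reading to an assistant in the same practice does not ensure blinding either, although it does separate the reading from the counselling relationship.

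**Conclusion.** The point holds as a weakness in how a primary outcome is measured. Allocation-aware OPs, or assistants not described as blinded, take the waist readings; no described safeguard removes error that differs by arm; and the article states no use for the independent readings. The size is unknown. If the differential error were 0.5 cm, the estimate would move by one third of the target, and the false-positive rate would be 18% without clustering or 8% with ICC 0.20. These figures rest on assumed errors and illustrate sensitivity; they are not evidence that bias occurred. At an assumed difference SD of 2 cm the independent sample could reveal a bias of about 1 cm or more, but could not rule out 0.5 cm. The matter deserves action because the main changes are cheap, not because the result is shown to be wrong.

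**What to change.** 1. Where an assistant is already available, have the assistant rather than the counselling OP take the 6-, 12- and 18-month waist readings, without sight of earlier values and, where possible, unaware of allocation. Cost: a scheduling instruction.
2. Keep the independent researcher unaware of allocation, and say so. Cost: none beyond organisation.
3. Prespecify a comparison, by arm, of the routine reading (OP or assistant) minus the independent reading. Report baseline, before counselling starts, separately from follow-up, with confidence intervals that account for clustering by OP, and present the waist effect alongside it as a sensitivity check. Cost: a short analysis of data already collected.
4. State in advance that the check can reveal a large bias but cannot exclude a small one, and that any calibration of the effect by arm is exploratory.
5. Add unblinded waist measurement to the limitations in the Discussion.

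If a full protocol or SAP already covers items 2 and 3, a sentence in the article saying so is enough.

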#### Primary outcome measures

##### Waist circumference

Waist circumference is measured as midway between the lower rib margin and the iliac crest to the nearest 0.1 cm [59,62]. Participants are measured in standing position without heavy outer garments and with emptied pockets, breathing out gently. To standardize waist circumference measurement, OPs or assistants were provided with a Seca 201 waist circumference measure (Seca, Hamburg, Germany). Additionally, waist circumference is measured in a random sample of workers (10-20%) at each measurement by an independent researcher.

